#### Statistical analysis of secondary objectives

*Self-reported medication adherence*. Self-reported adherence scores, collected at baseline, 3, 6, and 9 months, will be analyzed using GLMMs. These models will account for correlations between repeated measures across the different time points and clustering effects within facilities. The percentage of adherence in the intervention versus control groups will be compared, with adjustments made for potential confounders such as age, sex, and ART duration.

*Viral load suppression*. The proportion of patients achieving viral load suppression (VLS) at baseline, 3, 6, and 9 months will be modeled using logistic regression, adjusted for cluster effects. A comparison between the intervention and control groups will be made, considering time effects and covariates. The percentage of participants in each group who achieve viral suppression will be reported, and changes over time will be assessed.

*Social engagement*. Social engagement scores (SES) from the SSQ6 will be compared across time points (baseline, 3, 6, 9 months) using mixed-effects models. Participation in online communities will be tracked and compared to baseline scores to assess whether the intervention effectively improves social engagement. Differences in social engagement over time will be explored, with subgroup analyses based on age, sex, and baseline social support.

*Portal use and engagement metrics*. The frequency of portal logins, time spent on the portal, and functionalities accessed will be analyzed using descriptive statistics. Regression models will be used to explore relationships between portal use and adherence, activation, and viral suppression outcomes. Portal use will be summarized as engagement metrics (e.g., total logins, average time spent) and correlated with clinical outcomes, including adherence and viral suppression.

*Usability and acceptability scores*. Usability scores from the MAUQ and the custom-designed acceptability survey will be analyzed using descriptive statistics and compared across subgroups (age, sex, ART duration). Generalized linear models will be used to explore the association between usability scores and primary or secondary outcomes. Usability and acceptability will be assessed and reported, with particular attention to how these factors influence engagement with the platform.

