### Study design

This is a multicenter stepped wedge cluster randomized trial designed to evaluate the impact of the myCareHub patient portal on improving patient activation and clinical outcomes among HIV- positive AYP aged 15–24 years. Participants will be recruited from 47 EMR-enabled ART clinics (Table 1).

**Table 1 pdig.0000380.t001:** PICOT framework.

Population	Adolescents and young persons aged 15–24 years, who are living with HIV and are receiving care at an EMR-enabled Anti-Retroviral Treatment (ART) site. All participants will have ready access to a smartphone, which is necessary for using the myCareHub portal.
Intervention	Implementation and testing of the myCareHub patient health portal. This portal is designed with several functionalities that support behavior change according to the COM-B framework. These include e-learning resources, an online patient diary, peer-to-peer networking, patient-reported outcomes, and personalized care triggered by interaction with healthcare providers (HCPs).
Comparator	Standard of care patient engagement strategies, which involve traditional in-person clinic visits, standard ART support, and typical adherence and social engagement practices without the use of the myCareHub digital health portal.
Outcome	The primary outcome of the study is patient activation, which will be measured using the Patient activation measure (PAM). Secondary outcomes include viral load suppression, social engagement (assessed using the Social support questionnaire [SSQ6]), self-reported ART adherence, and portal usage metrics (e.g., login frequency, time spent, interaction with portal features).
Time	The study will span a total of 15 months. Initially, there will be a control period of 3 months, during which clusters will receive standard care. Intervention sequences will be rolled out every 3 months, with measurements taken at baseline and every three months for each cluster. After all clusters have received the intervention, a 6-month observation period will follow.

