### Justification for the stepped wedge design

The stepped wedge design was chosen to mitigate contamination bias. In a facility-based setting, randomizing individuals to control or intervention groups within the same facility would result in unintentional exposure of the control group to the intervention. The staggered implementation across clusters also enables continuous refinement of the myCareHub platform based on feedback from earlier clusters, thus improving the intervention over time.

A minimum sample of 480 AYP will be recruited into 16 clusters using a stepwise design, with three-month intervals between successive steps (Table 2).

**Table 2 pdig.0000380.t002:** Study design—cluster randomized trial utilizing a stepped wedge design with 16 clusters and 3 sequences.

CLUSTERS (11–16)	CONTROL	T0.: Baseline survey: Demographics, clinical enquiry, baseline PAM, adherence, VLS, social engagement scores on SSQ6, cluster level retention, cluster VLS.	CONTROL	T1 survey: 3 Mo PAM, adherence, VLS, portal measures: TB ICF, PHQ-9, CRAFFT, SGBV screening, Contraceptive use intention. Feedback on portal, cluster level retention, cluster VLS.	CONTROL	T2 survey: 3, 6 Mo PAM, adherence, VLS, retention, portal measures: TB ICF, PHQ-9, CRAFFT, SGBV screening, Contraceptive use intention. Feedback on portal, cluster level retention, cluster VLS.	INTERVENTION	T3 survey: 3, 6, 9 Mo PAM, adherence, VLS, retention, portal measures: TB ICF, PHQ-9, CRAFFT, SGBV screening, Contraceptive use intention, feedback on portal, cluster level retention, cluster VLS.	INTERVENTION	T4 survey: 6,9 & 12 Mo PAM, adherence, VLS, MAUQ, acceptability score, portal measures: TB ICF, PHQ-9, CRAFFT, SGBV screening, Contraceptive use intention, feedback on portal, cluster level retention, cluster VLS.
CLUSTERS (6–10)					INTERVENTION					
CLUSTERS (1–5)			INTERVENTION							
**TIME**	**TO**	**2 weeks**	**T1** **Mo 1–3**	**2 weeks**	**T2** **Mo 4–6**	**2 weeks**	**T3** **Mo 7–9**	**2 weeks**	**T4** **Mo 10–12**	**2 weeks**

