### Outcome measures

Outcome parameters will be measured at the individual level at pre-specified time points: baseline, every 3 months, and end-line (Table 5). These measurements will be captured using digitized case report forms (CRFs) to ensure accuracy and consistency in data collection.

**Table 5 pdig.0000380.t005:** Summary of outcome variables and analysis measures.

Variable	Definition	Units	Source	Measurement Level	Measurement Period	Comparison Groups	Analysis
PAM	Patient activation measure	100-point scale	PAM-13	Individual	Baseline, 3, 6 and 9 months	Intervention versus Control	Mean change in PAM
Self-reported medication adherence	Estimate of adherence on 0–100% scale	Proportion	Visual analogue scale and adherence questionnaire	Individual	Baseline, 3, 6 and 9 months	Intervention versus Control	% adherence
Viral load suppression (VLS)	Proportion with viral load below detection limit	Proportion	Electronic medical record	Individual	Baseline, 3, 6 and 9 months	Intervention versus Control	% VLS
Cluster retention	Active in care at the end of reporting period/active at the beginning of the period*100	Proportion	Program data	Cluster	Baseline, 3, 6 and 9 months	Intervention versus Control	% retention
Cluster VLS	Percent viral load suppression within cluster	Proportion	Program data	Cluster	Baseline, 3, 6 and 9 months	Intervention versus Control	% VLS
Mobile health application usability score	Numerical score	Mean score	mHealth App Usability Questionnaire (MAUQ)	Individual	End-point	Intervention	Mean scores
Mobile health service acceptability score	Likert-like scale and text	Sub-section scores	Custom acceptability tool	Individual	End-point	Intervention	Mean scores
Social support	Six questions on social supporters	Number of supporters and ratings of support	Social support questionnaire-6 item (SSQ-6)	Individual	Baseline	Intervention	Baseline SSQ-6 scores
Tuberculosis (TB) intensified case finding tool (ICF)	4 questions each scoring 0 or 1	0–4	Portal TB ICF tool, Paper-based TB ICF tool, Program reports	Individual	Continuous	Intervention versus Usual care	% cases diagnosed
							Median time to TB diagnosis
Screening for depression	9 questions each scored 0–3 for total possible score of 27	0–27	Portal patient health questionnaire (PHQ-9)	Individual	Continuous	Intervention versus Usual care	% cases diagnosed

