#### Social engagement score

The SSQ6 (Social Support Questionnaire—Short Form) is a well-established tool used to assess perceived social support availability. This tool, which is freely available for research use, measures the number of available supports and rates the participant’s satisfaction with that support [17]. We will track user engagement in online communities and compare it with baseline social engagement scores from the SSQ6. This will involve collecting quantitative data on user interactions and activity levels.

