## Results

This study will assess the impact of myCareHub on patient activation, medication adherence, social engagement and viral load suppression among AYP living with HIV. We anticipate improvements in these areas:

Patient activation—we expect that regular interaction with health diaries, reminders, and screening tools through the myCareHub platform will lead to increased PAM scores in the intervention group, indicating higher levels of patient engagement and activation in managing their health.Social engagement—increased use of online communities through the platform is expected to boost SSQ6 social engagement scores, particularly among those who may face barriers to in-person social interactions.Adherence and viral load suppression—with regular notifications and health management tools, we expect higher medication adherence rates and improved viral suppression among participants who use the portal consistently compared to those in the control group.

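### Social engagement (SSQ6) is to be modelled at baseline, 3, 6 and 9 months but is scheduled only at baseline, so no effect on this secondary outcome can be estimated under the stated schedule

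*Protocol article*

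**What the plan says.** **Analysis and claims.** The PICOT table (Table 1) lists social engagement, assessed with the SSQ6, among the secondary outcomes, and the abstract also names it as one. Under Statistical analysis of secondary objectives: "Social engagement scores (SES) from the SSQ6 will be compared across time points (baseline, 3, 6, 9 months) using mixed-effects models". The same paragraph plans subgroup analyses of differences over time. It also says participation in online communities will be compared with baseline scores to judge whether the intervention improves social engagement. The Results section predicts that greater use of online communities "is expected to boost SSQ6 social engagement scores".

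**Collection.** Three places say when the SSQ6 is given or used:

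- Table 5, Social support row: the measurement period is baseline, the comparison group is intervention, and the analysis is "Baseline SSQ-6 scores".
- Table 2: the T0 survey contains "baseline PAM, adherence, VLS, social engagement scores on SSQ6, cluster level retention, cluster VLS". The T1 entry reads "T1 survey: 3 Mo PAM, adherence, VLS, portal measures: TB ICF, PHQ-9, CRAFFT, SGBV screening, Contraceptive use intention", followed by portal feedback and cluster-level data. The SSQ6 is absent there and from T2, T3 and T4.
- Social engagement score (Study tools): "We will track user engagement in online communities and compare it with baseline social engagement scores from the SSQ6".

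**The concern.** The analysis needs SSQ6 scores at four time points and in both conditions. The instrument schedule provides one time point, before any cluster has crossed over. If the tables govern what sites do, a declared secondary outcome will have no post-baseline data. A predicted rise in SSQ6 could be neither confirmed nor refuted.

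The remaining comparison, online activity against baseline SSQ6, could then be reported as evidence of improved social engagement, which it cannot be. The loss would also be permanent: an SSQ6 assessment missed in a survey window cannot be recovered, and control-period values are gone once a cluster crosses over.

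**Working it through.** The plan gives no figure to reproduce on this point. The check sets the schedule beside the analysis and then asks what the stepped-wedge model can estimate from the data scheduled.

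**Step 1. Is the baseline-only entry shorthand?** Rows of Table 5 compared:

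| Outcome | Measurement period | Comparison |
|---|---|---|
| PAM | Baseline, 3, 6, 9 months | Intervention vs control |
| Self-reported adherence | Baseline, 3, 6, 9 months | Intervention vs control |
| Individual VLS | Baseline, 3, 6, 9 months | Intervention vs control |
| SSQ-6 | Baseline | Intervention |

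The SSQ-6 row differs in period, in comparison group and in stated analysis. Table 2 also itemises instruments by survey; for example, the MAUQ and the acceptability score appear only at T4. Leaving the SSQ6 out of T1 to T4 is therefore an instruction that sites could follow.

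**Step 2. What is estimable with SSQ6 at T0 only?** Inputs: 16 clusters, all starting in control; sequences cross over at T1, T2 and T3 (Table 2). The fixed part of the model is an intercept, period effects and an intervention indicator.

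- Cluster-periods: 16 × 1 = 16.
- Cluster-periods under intervention: 0.
- Columns: intercept and intervention indicator = 2. The indicator is zero throughout, so the rank is 1 of 2.

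The intervention effect is not identified. With a single period there is no time contrast either. Table 5's intervention comparison group has no members at baseline.

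**Step 3. What changes if SSQ6 is also collected at T1, T2 and T3?** Cluster-periods: 16 × 4 = 64. Sequences 1, 2 and 3 contribute 3, 2 and 1 intervention periods per cluster.

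- Table 2 split (5, 5, 6 clusters): 5×3 + 5×2 + 6×1 = 31 of 64 under intervention.
- Table 4 split (6, 6, 4 clusters): 6×3 + 6×2 + 4×1 = 34 of 64.
- Columns: intercept, 3 period effects, intervention = 5. The rank is 5 of 5 under both splits.

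The intervention effect and the time contrasts are then estimable.

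**Step 4. What does T4 add?** Cluster-periods: 16 × 5 = 80, with 31 + 16 = 47 (Table 2) or 34 + 16 = 50 (Table 4) under intervention, and rank 6 of 6. All 16 added cluster-periods are under intervention. T4 therefore adds length of exposure, notably for the third sequence, but no concurrent control data.

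**Step 5. Can online activity stand in for follow-up SSQ6?** The SSQ6 yields a number of supporters and ratings of support. Online engagement in Table 5 is usage logs, time spent and features used, listed for the intervention only. The two share no scale, so their difference is not a change score. Without a control-period value there is also no between-condition contrast. An association between the two could be described, but it would not show improvement.

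**The case against.** The strongest reply is that the document conflicts with itself, so baseline-only collection is not settled. The analysis paragraph names four SSQ6 time points. The Time row of Table 1 speaks of measurement at baseline and every three months. The opening of Outcome measures says something similar, and the abstract lists social engagement among the baseline measurements before mentioning later checks. On that reading the tables are simply incomplete.

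Part of this stands: non-estimability is conditional on Tables 2 and 5 governing collection. But none of the general statements assigns the SSQ6 to a later visit. The one in Outcome measures refers to Table 5, which gives baseline only for the SSQ6. The abstract's months are 3, 6 and 12, which do not match the 3, 6 and 9 of the analysis. If repeat collection was intended, Tables 2 and 5 are wrong and still need correcting.

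Four further points are fair:

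- The primary outcome, PAM, is unaffected, as are the sample size and randomization.
- The analysis text asks for nothing beyond 9 months, so T4 collection goes further than the stated model needs.
- Withdrawing the longitudinal SSQ6 analysis would be an equally coherent resolution, and the Table 5 row is consistent with it.
- The article presents the online-activity comparison beside the mixed model, not as its replacement. It becomes the only remaining comparison if no follow-up SSQ6 is collected.

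These points bear on the choice of remedy and on priority. They do not remove the contradiction.

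**Conclusion.** The concern holds. Under the instrument-specific schedule, none of the three post-baseline SSQ6 measurements that the mixed model needs (3, 6 and 9 months) is planned. The data would be 16 cluster-periods, all in control, from which neither a change over time nor an intervention effect can be estimated. This is the same under the Table 2 and Table 4 cluster splits.

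The conclusion assumes that sites follow Tables 2 and 5, which are the only places that assign the SSQ6 to specific surveys. It is a contradiction within the article, not detail deferred to an analysis plan. It is confined to a secondary outcome, but it must be fixed before the affected surveys are run because the data cannot be collected retrospectively.

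**What to change.** **Preferred: collect the SSQ6 repeatedly.**

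- Add the SSQ6 to the T1, T2 and T3 surveys in Table 2, in every cluster whether in control or intervention. Adding T4 as well covers the final period; if so, extend the analysis sentence to 12 months.
- Change the Table 5 row to repeated measurement, intervention versus control, with the between-condition difference as the analysis.
- Analyse it with the mixed-model structure used for PAM (period, intervention, cluster and participant effects). Say whether the number of supporters or the satisfaction rating is the outcome, since one model form may not suit both.
- Report online-community activity as a usage metric only, and drop the claim that comparing it with baseline SSQ6 shows improvement.

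**Alternative: keep the SSQ6 at baseline only.** Withdraw the longitudinal analysis, use the SSQ6 as a baseline covariate or descriptor, and remove SSQ6 social engagement from the secondary outcomes in the abstract and Table 1 and from the expected improvements in Results.

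**Cost.** The preferred route needs a protocol amendment and a six-question instrument, each question asking for supporters and a rating, at surveys already scheduled. With 480 participants and no attrition, that is 480 × 3 = 1,440 extra administrations for T1 to T3, or 480 × 4 = 1,920 with T4. The alternative needs text changes only, but gives up the outcome. If any survey round has already taken place without the SSQ6, that round is lost, and the analysis should state which periods remain.

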**Abbreviations**: TO–baseline, T1 –time period 1, T2 –time period 2, T3 –time period 3, T4 –time period 4. Mo–month. PAM–patient activation measure. VLS–viral load suppression. SSQ6- social support questionnaire short form. MAUQ–mHealth App usability questionnaire. TB ICF–tuberculosis intensified case finding. PHQ-9 –patient health questionnaire– 9 items, SGBV–sexual and gender-based violence, CRAFFT–car, relax, alone, forget, friends, trouble. **NB**: The third sequence is extended to ensure that the final stratum completes a minimum of six months, which is the recommended duration for adequately assessing patient activation.

To minimize heterogeneity between clusters, stratification was applied based on size (small, medium, large), sex (male, female), and viral load suppression (VLS). This stratification created comparable blocks of clusters prior to randomization, ensuring balance across the intervention groups (Table 3). Clusters were then randomly assigned to one of three sequences for the time of crossover from control to intervention using a computer-generated random number list (Table 4). Each cluster will begin in the control period and transition to the intervention at staggered intervals, with clusters randomized to groups of five or six. Each intervention sequence will last three months, with a two-week interval between sequences to allow for baseline measurements and smooth implementation of the intervention. The third sequence will extend for six months to allow for additional measurements (Table 2).

**Table 3 pdig.0000380.t003:** Sub-counties by key attributes.

Sub-county	Number of AYP ^b^	Size strata	VLS ^a^ 15–19	VLS 20–24	Cohort retention	Males (%)
Thika town	632	Large	80%	90%	89%	41%
Ruiru	330		84%	89%	68%	25%
Kiambu town	205	Medium	86%	89%	100%	32%
Kiambu Central	176		86%	90%	84%	55%
Gatundu South	166		61%	90%	50%	40%
Juja	146		91%	82%	67%	35%
Kiambaa	123		87%	91%	100%	27%
Kirinyaga South	116		91%	87%	88%	53%
Githunguri	113		85%	89%	100%	27%
Kabete	110		94%	94%	100%	23%
Gatundu North	107		92%	89%	100%	40%
Limuru	103		90%	100%	100%	35%
Kirinyaga West	88	Small	81%	92%	74%	37%
Kikuyu	73		100%	90%	100%	16%
Kirinyaga East	58		100%	86%	87%	57%
Lari	51		100%	91%	100%	23%
Kirinyaga North	50		60%	68%	88%	48%

^a^ viral load suppression

^b^ adolescents and young persons

**Table 4 pdig.0000380.t004:** Randomization of clusters into sequences.

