#### Variable selection

Variables such as age, sex, occupation, duration on ART, presence of a treatment buddy, and last viral load will be included based on their relevance to the study objectives and previous literature. The primary outcome will be the change in patient activation measure (PAM) at 6 and 9 months. Changes in PAM score will be analyzed with respect to intervention and control groups, stratified by age category (15–19 vs. 20–24), sex (male vs. female), and duration on ART (<12 months vs. >12 months).

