#### Handling of potential confounding variables and assumptions

Confounding variables identified through exploratory analyses, such as sociodemographic factors and baseline clinical characteristics, will be included in the model to adjust for their effects on PAM scores. Model diagnostics will be performed to ensure appropriate model fit, including checks for residuals and potential overdispersion. Random effects will account for individual variations and cluster effects. The assumptions of GLMMs, including the normality of random effects and the appropriate link function, will be tested using diagnostic plots and statistical tests.

Sensitivity analyses, including the use of causal inference methods, will be conducted to assess the effect of differential patient and cluster characteristics over time, and attrition on the comparison between intervention periods. These analyses will also evaluate the robustness of findings, including the handling of missing data, such as treating PAM scores of 0 and 100 as missing values.

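### The planned correlation of cumulative portal use with outcomes names no scaling for access time and no baseline adjustment, so it could be spurious in either direction

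*Protocol article*

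**What the plan says.** The paragraph on portal use and engagement metrics (Statistical analysis of secondary objectives) plans descriptive statistics and two analyses that link use to outcome. The first is a set of regressions: "Regression models will be used to explore relationships between portal use and adherence, activation, and viral suppression outcomes". The second is a correlation: "Portal use will be summarized as engagement metrics (e.g., total logins, average time spent) and correlated with clinical outcomes, including adherence and viral suppression". The paragraph lists no covariates. The adherence paragraph in the same section names age, sex and ART duration, and the viral suppression paragraph mentions time effects and covariates.

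Covariates appear elsewhere, around the PAM outcome. Variable selection says "Variables such as age, sex, occupation, duration on ART, presence of a treatment buddy, and last viral load will be included". The confounding section says that confounders, including baseline clinical characteristics, "will be included in the model to adjust for their effects on PAM scores".

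Access to the portal is staggered by design: "Each cluster will begin in the control period and transition to the intervention at staggered intervals". The note to Table 2 adds: "The third sequence is extended to ensure that the final stratum completes a minimum of six months". The Discussion accepts that people at ease with technology may use the portal more and that this could distort results. The Results section expects "improved viral suppression among participants who use the portal consistently compared to those in the control group".

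**The concern.** How much a participant uses the portal is decided after randomisation, by the participant. Someone already adherent or suppressed may log in more, or someone who is struggling may do so. Either pattern produces an association between use and outcome with no portal effect behind it.

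The one count named as an example, total logins, also grows with months of access, which the design makes unequal.

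The introduction says the study is meant to inform HIV programming and digital health policy. An association between heavy use and viral suppression could be read there as evidence that more use works, and the wording in Results about consistent users encourages that reading.

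**Working it through.** The protocol gives no figure for this analysis, so there is none to reproduce. The sample size does reproduce: 27 / (1 - 0.10) = 30 per cluster, 30 x 16 = 480, and 186 + 170 + 124 = 480 (Table 4).

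**Inputs from the protocol**
- Access by the end of T4 (Table 2, ignoring the two-week survey windows): 12, 9 and 6 months for sequences 1, 2 and 3.
- n = 480 in 16 clusters, with 186, 170 and 124 participants by sequence (Table 4).
- ICC 0.02 and individual autocorrelation 0.8 (Sample size estimation). These are stated for PAM and are assumed here for a generic continuous outcome.

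**Assumed, because the documents give no value**
- r, the correlation between log login rate and the stable individual part of the outcome: -0.3 to 0.3.
- Login rate: median 4 per month, SD 0.5 on the log scale, Poisson counts.
- Secular trend: -0.3 to 0.5 SD per 12 months.

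**Model.** Outcome variance is 1 = 0.02 (cluster) + 0.98 x 0.8 = 0.784 (stable individual) + 0.98 x 0.2 = 0.196 (visit noise). The portal effect is zero. The outcome is regressed on standardised log total logins with cluster-robust standard errors, two-sided 5%, 400 simulated trials per scenario. The Monte Carlo standard error at 38% is sqrt(0.38 x 0.62 / 400) = 2.4 points.

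**Step 1: self-selection, outcome at the common end date.** Each cell gives the mean slope in SD and the share of trials with a significant association of the sign shown.

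| r | Unadjusted | Adjusted for baseline | Baseline and months of access |
|---|---|---|---|
| -0.3 | -0.220; 99.75% negative | -0.044; 37.5% negative | -0.062; 51.75% negative |
| 0 | -0.001; 2.5% positive | 0.000; 3.5% positive | -0.001; 3.75% positive |
| 0.1 | 0.078; 38% positive | 0.016; 12% positive | 0.018; 11.25% positive |
| 0.2 | 0.149; 87.25% positive | 0.031; 23.5% positive | 0.035; 25% positive |
| 0.3 | 0.222; 99.5% positive | 0.046; 44% positive | 0.060; 49.25% positive |

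**Step 2: hand check at r = 0.3.** If total logins measured login rate perfectly, the slope would be r x sqrt(0.784) = 0.3 x 0.885 = 0.27. Unequal access and count noise dilute this to the simulated 0.222. After baseline adjustment, with c = 0.222 and a correlation between visits of 0.02 + 0.784 = 0.804, the slope is c(1 - 0.804) / (1 - c^2) = 0.222 x 0.196 / 0.951 = 0.046, as simulated. The remainder is there because one noisy baseline captures only part of the stable trait.

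**Step 3: unequal access alone (r = 0).** At a common end date the mean slope is about 0 and total rejection is 5% to 10% over four runs. Sequence is randomised, so months of access does not bias that analysis.

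If all intervention visits are pooled without a time term, a secular trend does bias it. Significant positive associations occur in 9.5%, 14.25%, 23.5% and 47.25% of trials for trends of 0.1, 0.2, 0.3 and 0.5 SD per 12 months. With a trend of -0.3, 24.75% are significant and all are negative. Adjusting for months of access, or for baseline and calendar time, brings total rejection back to between 4% and 8.25%.

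**Step 4: late entry and dropout (not simulated).** The sample size section allows extra recruitment to offset losses, and the Discussion expects dropout among people with poor device or internet access. Both groups accrue fewer total logins simply through less time, and dropout may be related to outcome.

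**The case against.** The strongest reply is that silence in a condensed article does not mean an unadjusted analysis. Regression models are planned beside the correlation, the opening of Statistical methods applies mixed models to primary and secondary endpoints, last viral load is a listed covariate, and a fuller covariate list may sit in a document not shown. This stands. A reader might infer that the plan rules out adjustment, but the text does not say so. What remains is that it states a correlation and names a cumulative count for it.

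Total logins is only an example; login frequency and average time spent are also named. That is fair, and it means the fix is to settle on one time-scaled metric.

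Four other stronger readings are tempting and are not supported:
- *The analysis would show a benefit.* The sign and size depend on who logs in more, which the documents do not give. At r = 0 there is no bias, and at negative r it reverses.
- *Unequal access alone creates bias.* Step 3 shows it does not at a common end date.
- *The trial discards its randomisation.* The sentence in Results is an expectation. Table 5 and the planned adherence and suppression analyses compare intervention with control.
- *The protocol presents a causal dose-response analysis.* Its own terms are exploratory, and the Discussion discloses self-selection.

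Finally, the calculation borrows PAM's correlations for a continuous outcome, whereas the quoted sentence concerns adherence and viral suppression. The mechanism carries over to those outcomes; the percentages may not.

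**Conclusion.** The point holds as a caution about an exploratory secondary analysis. As worded, the use-outcome correlation is open to self-selection and, in some forms, to exposure-time confounding, and this paragraph names no protection against either.

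The size rests on the assumed r. With a null portal, r from 0.1 to 0.3 gives a false positive association in about 38% to 99.5% of trials. Baseline adjustment lowers this to 12% to 44%, and at r = 0.3 it cuts the false slope from 0.22 SD to about 0.05 (0.06 with months of access added). It should therefore not be presented as a cure, and the result can be reported only as an association.

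The primary and randomised secondary comparisons are unaffected.

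**What to change.** 1. In the portal-use paragraph, define use as logins and minutes per 30 days of access, counted from the participant's own crossover.
2. Replace the simple correlation with a model restricted to intervention periods. Include the baseline value of the same outcome, cluster, calendar period and months since crossover. Enter cluster as a random effect: with fixed cluster effects, months since crossover would be almost wholly determined by cluster and period.
3. State that the result is a non-causal association and that residual self-selection is expected after adjustment.
4. In Results, state the expected gain in adherence and suppression for all participants in intervention periods against control periods, whatever their use, to match Table 5.

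The cost is wording. Baseline PAM, adherence and viral suppression are collected at T0, and logins and time spent are logged automatically. The downside is that the usage associations will look weaker.
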